### Statistical analyses

Data will be entered, screened, and analysed using SPSS Version 21 [25]. A RMANCOVA will be implemented to explore differences between the conditions over time, and calculate effect sizes to investigate the treatment effect. An intention-to-treat methodology will be applied via multiple imputation. The qualitative data obtained from the focus groups will be analysed according to the Interpretative Phenomenological Analysis (IPA) method (for example, [50, 63]). This will be achieved by transcribing the data verbatim from audio recordings into text. The text transcripts will be read several times to extract emerging codes, which will then be transformed into themes [50]. Themes are likely to identify both something of importance to the participants, and also convey a meaning of their reflection [63]. These themes will form the basis for the qualitative results. Direct quotes from the participants will also be reported to highlight the thematic findings [63].

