## Methods/Design

### Trial design

This trial will follow the International CONSORT (Consolidated Standards of Reporting Trials) guidelines and evaluate conditions using a randomised control trial (RCT) design [56]. Participants who are eligible for the trial will be randomly allocated to one of three conditions: CBT-I, CBT-I-D, or PCG. Outcomes will be assessed at pre-intervention (week 0), post-intervention (week 8), and 3-month follow-up (week 20). Figure 1 illustrates the study’s design and expected participant flow chart.

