### Randomisation

The randomisation allocation process of participants to treatment groups will comply with CONSORT guidelines (for example, [37]). A block/cluster randomisation design utilising random permuted blocks with randomised block sizes will be implemented to randomly allocate each participant group to one of three conditions throughout the trial. Block randomisation is commonly used in small- to moderate-sized RCTs to ensure that approximately equal numbers of participant groups in the clustered context are allocated to each condition [67]. The computer-generated random allocations will be generated by an independent researcher at Federation University Australia and will be stored on a password-protected computer back-up to a secure university file server. Random allocation will occur after the pre-treatment assessments have been completed to ensure eligibility has been met. Each successive random allocation will be communicated to the principal investigator only when five to six eligible participants are ready to commence a group. Participants will be unaware of the study’s hypotheses or which group they have been randomly allocated. The co-therapists will not be blinded to the treatment conditions.

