### Sample size calculation

Statistical power analysis was based on an examination of treatment-time interactions in a repeated measures analysis of covariance (RMANCOVA) of the ISI measure [38], with adjustment for confounders. We specified an initial value of 18 points in the adjusted mean of the ISI score at pre-intervention [22]; a mean reduction of 10 points from pre- to post-intervention for the CBT-I treatment [22]; and a target value of two points difference between the pre-post changes for each of the three treatment conditions (that is, -8, −10, and −12 points, respectively) [43], with no further change at follow-up [43], and assuming a ‘within-treatments’ SD of 3.4 points [22]. This resulted in an effect size of 0.23. Under the assumptions of constant correlation over time (sphericity), with an estimated magnitude of *r* = 0.6 based on reported test-retest reliabilities of 0.79 [14] and 0.86 [76], and allowance for a design effect [16] of 1.07 due to clustering of participants within treatment groups (based on an assumed cluster size of five and an intra-class correlation of 0.017, [22]), with a significance level of 5 % and 80 % power, the required sample size calculated using GPower software [20] is *N* = 35 (33 × 1.07). Maintaining the same specifications, but focusing solely on the CBT-I and CBT-I-D conditions, the specific target difference of two points between the pre-post changes for these two particular treatments corresponds to an effect size of 0.13. In order to have 80 % power to detect this particular difference in a post hoc pairwise comparison, the required sample size is increased to *N* = 85 (78 × 1.07).

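### Whole therapy groups are randomised, but the named RMANCOVA has no therapy-group term, so its type I error is about 6% at the plan's own ICC if group effects arise during therapy

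*Protocol article*

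**What the plan says.** **Unit of randomisation.** The Randomisation section uses a block/cluster scheme "to randomly allocate each participant group to one of three conditions throughout the trial". Each allocation is released "only when five to six eligible participants are ready to commence a group". The target in Sample size calculation is 150 participants, or 10 groups in each of three conditions, which makes 30 randomised units. Participants in a group are also treated together for eight weekly sessions.

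**Clustering acknowledged.** Sample size calculation makes "allowance for a design effect [16] of 1.07 due to clustering of participants within treatment groups", from a cluster size of five and an ICC of 0.017.

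**Analysis.** Statistical analyses states: "A RMANCOVA will be implemented to explore differences between the conditions over time". Sample size calculation names the same method for the treatment-by-time interaction, and the only adjustment it mentions is for confounders. Neither section mentions a therapy-group term, a mixed model, cluster-robust standard errors or a group-level analysis.

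**Other descriptions.** The Abstract says block/cluster randomisation. The Trial design section says only: "Participants who are eligible for the trial will be randomly allocated to one of three conditions".

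**The concern.** The randomisation and the sample size both treat the therapy group as a source of correlation. The named analysis treats 150 participants as independent. The sample size section shows this directly: it takes the sample size for an RMANCOVA and then multiplies it by a design effect, a step that is needed only because the RMANCOVA does not allow for groups.

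Multiplying the sample size restores power. It does not change the error term of the test. If members of a group come to resemble each other during therapy, variation between groups is part of the difference between conditions but is under-represented in the error term. Intervals are then too narrow and p-values too small. This would affect both primary outcomes (ISI and GDS), including the central comparison of CBT-I-D with CBT-I. One or two groups that did unusually well or badly could pass for a treatment effect.

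**Working it through.** **Inputs from the protocol article:** 3 conditions, 10 groups per condition, 5 per group (up to 6), ICC 0.017, correlation over time r = 0.6 under sphericity, assessments at weeks 0, 8 and 20, significance level 5%. **Assumed here:** ICCs of 0.05 and 0.10 (sensitivity only), and a group effect that is absent at baseline and shared by weeks 8 and 20.

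**1. The plan's own figure.** Design effect = 1 + (m − 1) × ICC = 1 + 4 × 0.017 = 1.068, stated as 1.07. It reproduces. For the ISI, 33 × 1.07 = 35.3 (stated 35) and 78 × 1.07 = 83.5 (stated 85). With six per group the design effect is 1 + 5 × 0.017 = 1.085.

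**2. Degrees of freedom.** The interaction test at participant level has (150 − 3) × 2 = 294 error degrees of freedom under sphericity. Between randomised groups there are 30 − 3 = 27.

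**3. Simple formula.** Ignoring a design effect DE makes the standard error too small by a factor of 1/√DE, and the type I error becomes 2 × [1 − Φ(1.96/√DE)].
- ICC 0.017: DE 1.068, factor 0.968 (about 3% too small), type I error 5.8%.
- ICC 0.05: DE 1.20, factor 0.913, type I error 7.4%.
- ICC 0.10: DE 1.40, factor 0.845, type I error 9.8%.

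**4. On the scale of change.** The repeated-measures test removes stable differences between participants from its error, so a group effect that arises after baseline weighs more. Set the participant variance to 1 at each visit. The mean of the two later visits minus baseline has participant variance (1 − 0.6) × (1 + 1/2) = 0.6. The group variance is ICC/(1 − ICC), which is 0.0173 at 0.017. The ICC of the change is 0.0173/(0.6 + 0.0173) = 0.028, so DE = 1 + 4 × 0.028 = 1.112 and the type I error is 6.3%. The same steps give 8.8% at ICC 0.05 and 12.4% at 0.10.

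**5. Simulation** of the treatment-by-time F test under no treatment effect (40,000 runs per setting, five per group):

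| ICC | Three conditions | Two conditions | Test on group means |
|---|---|---|---|
| 0.017 (plan) | 6.2% | 5.9% | 5.0–5.1% |
| 0.05 (assumed) | 8.8% | 7.8% | 4.9–5.1% |
| 0.10 (assumed) | 13.6% | 11.0% | 4.9–5.1% |

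Six per group at ICC 0.017, three conditions: 6.5%.

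**6. Opposite case.** If the group effect is already present at baseline and constant over the three visits, the same F test rejects in 5.0% of runs at ICC 0.017. It cancels from the interaction.

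**The case against.** **The excess is small on the plan's own figures.** This stands. At ICC 0.017 it is about one percentage point. The larger percentages need ICCs of three to six times the planned value, which the article does not support. They show only how the error would grow if the single borrowed ICC proved too low.

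**The direction is conditional.** This also stands. A reader might infer that the type I error must exceed 5% for every comparison. The documents do not support that, since a stable group effect cancels. However, the article gives reason to expect effects that arise during therapy. Its Interventions section chose groups partly for peer support and motivation, and it links group connectedness to treatment effect. The members of a group also share co-therapists.

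**It belongs in an SAP.** Details such as the covariance structure do. The choice of method does not, because the article fixes it and it conflicts with the article's own randomised unit. The article never says in words that participants are independent. That follows from the named method and from the design effect applied to its sample size.

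**A random group effect may often be estimated as zero.** With 30 groups of five and ICC 0.017, this would happen in about 42% of balanced trials (a single-visit calculation). This is a fair caution about relying on the variance estimate alone, and a reason to allow the group-means alternative.

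**Two further inferences to avoid.** A reader might infer that the article conceals the clustering behind individual allocation. It does not: the Abstract and the Randomisation section both state it, and only Trial design is generic. A reader might also size the error from a baseline-adjusted ANCOVA that ignores groups (6.7%, 10.6% and 14.7% at the three ICCs). The plan treats baseline as a repeated visit and does not name the baseline score as a covariate, so those figures are not for the stated analysis.

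**Conclusion.** The point holds in this form: the named analysis does not match the randomised unit, and the design effect enters the sample size but not the inference. If group effects arise during therapy, the true type I error of the nominal 5% treatment-by-time test is about 6% at the plan's ICC of 0.017. Standard errors are then about 3% too small by the plan's own design effect, or about 5% on the scale of change (1/√1.112 = 0.948). The range of about 8 to 9% at ICC 0.05 and about 10 to 14% at ICC 0.10 is sensitivity only. These figures rest on r = 0.6, equal groups of five, a group effect shared by both later visits, and an RMANCOVA run without a group term. The fault is real and cheap to correct, but modest on the plan's own figures. It should be fixed.

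**What to change.** In Statistical analyses, replace the RMANCOVA with an analysis that respects the therapy group. One suitable choice is a linear mixed model with:
- condition, time and condition-by-time as fixed effects;
- a random effect for therapy group that can arise after baseline (for example group-by-time), because a constant group intercept alone would model only the part that cancels;
- correlation over time within participant;
- small-sample degrees of freedom suited to about 30 groups.

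An analysis of group-level means is an acceptable alternative and held about 5% in every setting checked.

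Keep therapy group in the multiple imputation model, and report the observed ICC for both primary outcomes. Align the Trial design section with the group randomisation described in the Abstract and the Randomisation section.

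The cost is a change of wording and slightly wider intervals. Clustering requires no extra participants, because the design effect is already in the sample size.

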### Ethics approval and trial registration

This trial will be conducted in accordance with the ethical guidelines outlined in the National Statement on Ethical Conduct in Human Research [45]. Ethics approval for this project has been granted by the Federation University Australia Human Research Ethics Committee (E-14-042), the Latrobe Regional Hospital Human Research Ethics Committee (2014-02-LNR), and the Peninsula Health Human Research Ethics Committee (HREC-15-PH-4). The trial has also been registered with the Australian New Zealand Clinical Trial Registry, ACTRN: 12615000067572.

## Discussion

This paper describes the study protocol for the development and evaluation of a CBT program for older adults with comorbid insomnia and depression. The results from this trial will represent a significant step forward in this field and assist in advancing CBT-I for older adults receiving mental health services for depression. Several important clinical implications could result from this project.

One of the primary aims is to evaluate whether CBT-I is effective among a complex sample of older adults with comorbid insomnia and depression in a community mental health setting. We predict that CBT-I will be more effective at reducing insomnia severity compared to the PCG. If this hypothesis is supported, it will demonstrate that CBT-I is helpful at reducing insomnia severity for older adults with depression in a community mental health setting. This evidence will add to a growing research base that suggests CBT-I needs to be considered as a treatment option for individuals with comorbid insomnia [30, 66, 71].

Since previous research has suggested that comorbid insomnia is often misunderstood and inadequately treated [18, 40, 62], education and training play a vital role to address this disparity between research and clinical practice. This could involve providing workshops to mental health practitioners to raise their awareness of addressing comorbid insomnia during the assessment, case conceptualisation, and treatment planning phases. To ensure older adults with comorbid insomnia have access to this form of psychological treatment, mental health services could also consider training a therapist on their multidisciplinary team in CBT-I, or at least source an external CBT sleep specialist as a referral option. These implications could potentially improve therapeutic outcomes for older adults receiving mental health services by ensuring clinicians are better equipped to address comorbid insomnia.

This project also plans to explore whether improving an older adult’s sleep pattern with CBT-I has an associated positive impact on their mood. Recent preliminary evidence suggests CBT-I can have a positive effect of depression levels [28, 32, 72]; however, these studies have substantial methodological limitations that restrict the generalisability of the results. Consequently, this study aims to test whether CBT-I generates greater reductions in depressive severity compared to a PCG. If the results indicate that CBT-I is more effective at improving depression compared to the control condition, aged psychiatric services could consider adding CBT-I as a regular treatment option for their clients presenting with comorbid insomnia and depression.

A unique feature of this trial involves testing an advanced form of CBT-I that includes additional strategies to address comorbid depression among older adults. Although recent studies (for example, [71]) have suggested that specifically designed CBT-I programs may produce better overall outcomes for targeted populations (for example, older adults with comorbid insomnia and depression), no study has tested whether an advanced CBT-I-D program is more effective than a standard CBT-I program. The results following this specific investigation could highlight that CBT-I is sufficient to address both insomnia and depression or indicate CBT-I-D is clinically indicated to better treat these conditions simultaneously. This result could guide future CBT-I treatment programs in relation to either broadening or lessening the scope of treatment.

Finally, we are interested in studying the participants’ experiences from taking part in a CBT trial for insomnia and depression. The information gained from a mixed methods design will provide an opportunity to gather rich, personal data through older adults that can either confirm or disconfirm the questionnaire outcome measures [13, 33]. This can open new avenues of explanation for particular findings that traditional quantitative measures cannot detect [47]. For example, results from the reflective focus groups may indicate participants benefitted from specific CBT strategies that would not be revealed through quantitative data [33]. In addition, participants may provide innovative feedback that is particularly relevant to the delivery of CBT-I among this complex aged population. Therefore, it is expected that the qualitative findings from this project will enhance the direction of future research in this field.

Despite the important implications that may result from this study protocol, the project will likely include limitations. First, no physiological measure of sleep (for example, polysomnography) will be assessed to cross-validate the clinical interview and self-report data. This means that the assessments throughout the trial will be reliant on subjective measures from the participants and researchers, as opposed to objective biological data. Since no standardised clinical diagnostic instrument has been established yet for the *DSM-V*, the authors updated existing *DSM-IV* diagnostic instruments (for example, MINI 6.0) to be consistent with the *DSM-V* diagnostic criteria. Finally, participant recruitment and retention rates could be negatively affected due to this population likely experiencing stronger symptoms of tiredness, hopelessness, and amotivation. Hence, recruiting participants and keeping them engaged throughout the program will likely create significant challenges. Notwithstanding these limitations, the results following this study protocol will likely contribute important knowledge that improves case formulation and treatment planning for older adults with comorbid insomnia and depression.

## Trial status

Recruitment began in August 2014 and will continue until June 2016.

## Abbreviations

CBT: cognitive behaviour therapy
CBT-I: cognitive behaviour therapy for insomnia
CBT-I-D: cognitive behaviour therapy for insomnia and depression
PCG: psycho-education control group
RCT: randomised controlled trial
